## Abstract

**Introduction::**

*Mibyeongbogam* (MBBG) is a mobile application developed for subhealth status self-management in the Republic of Korea. It aims to assess a user's subhealth status, and then to recommend relevant traditional Korean medicine (TKM)-based health-promoting strategies. The purpose of this study is to evaluate the feasibility and effectiveness of MBBG's employment for the subhealth management of general healthy adults.

**Methods::**

This is a prospective, open-label, parallel group, randomized controlled trial that will seek to enroll 150 healthy adults, aged 30 to 49 years old, from 2 hospitals in the Republic of Korea. The eligible participants will then be randomly allocated to either the MBBG or control group, at a 1:1 allocation ratio. The MBBG group will use the application for 12 weeks, while the control group will undergo no intervention. The awareness of subhealth status will be primarily assessed. Health promoting behaviors, quality of life, TKM-based health questionnaires, and physical examination results will be assessed as secondary outcomes.

**Discussion::**

The primary endpoint will be tested with a 2-sample *t* test, or a Wilcoxon rank sum test. Any other continuous variables will be tested via an analysis of covariance, while categorical variables will be tested by a Chi-squared or Fisher exact test. Repeated measure analysis of variance will be performed to explore any in-group differences. The results will be addressed with a 95% confidence interval. We expect that MBBG will be the 1st TKM-based mobile application to be feasible for primary care in subhealth management.

**Trial registration::**

CRIS (Clinical Research Information Service), KCT0003488, February 11, 2019

## Introduction

1

*Mibyeong* is a concept referring to subhealth status in traditional Korean medicine (TKM). This concept is usually used to mean a state in between health and disease. A person might complain of subjective symptoms or abnormal examination findings, but not be diagnosed with any disease, such as borderline hypertension or diabetes. This subhealth status does not require any specific treatment, but may carry with it a high risk for future disease development.^[1]^ Preventive medicine has been trying to find ways to manage this subhealth status.^[2]^ A survey involving 818 TKM practitioners showed that they often encountered patients with subhealth statuses, and these patients mostly complained of fatigue, pain, or digestion problems. However, it is also reported that only 23% people in the subhealth state go to see doctors to figure out what is happening with their bodies. About 73% to 80% of people who complained of either fatigue- or pain-related symptoms showed no improvements, after as long as 6 months.^[3]^ This is why TKM researchers have been trying to address the necessity of understanding,^[4]^ conceptualizing,^[1]^ and developing an instrument to identify subhealth states.^[5]^

*Mibyeongbogam* (MBBG) is a mobile application developed by the Korea Institute of Oriental Medicine, in Daejeon, within the Republic of Korea, to manage peoples’ subhealth statuses. It assesses an individual's state of health via a series of validated questionnaires, put together through several physical examination results, and then recommends how to, successfully, promote healthier lifestyles in TKM-based manners (meditation, exercising, herb teas, etc). Users can easily access the application via their smartphones, and can then be provided what they have to manage to improve their own general health, given information on their own health states.^[6]^

Clinical researchers have been trying to adopt mobile health technology aimed at positively changing health behaviors or to manage disease conditions. However, the evidence around it is not yet confirmed and the implementation of mobile applications for subhealth management is still rare.^[7]^ A previous study uncovered the possibility of a mobile application to help assess and manage youth mental health problems.^[8]^

The purpose of this study is to determine the effectiveness of MBBG employment for subhealth management by general healthy adults, and to assess its feasibility in implementing MBBG in practical ways.

## Methods

2

This study follows the Standard Protocol Items: Recommendations for Interventional Trials (SPIRIT) 2013 statement.^[9]^ The Institutional Review Board of the Kyung Hee University Korean Medicine Hospital at Gangdong, in the Republic of Korea, reviewed and approved this study protocol, as well as its informed consent form (KHNMCOH 2018-07-002-002) on September 11, 2018 (protocol version 1.2). The protocol has been registered in the Clinical Research Information Service (CRIS, https://cris.nih.go.kr/cris/en/, KCT0003488) on February 11, 2019. Any protocol amendments will be publicly reflected via CRIS.

### Objectives

2.1

The primary objective of this study is to compare the awareness around subhealth status between an MBBG group and a control group. Health promoting behaviors, physical markers, subjective health statuses (including a quality of life [QoL] scale) will be assessed and compared between the 2 groups. Based upon these results, the feasibility of the MBBG application in managing and preventing subhealth statuses within individuals will be assessed.

### Study design and setting

2.2

This is a prospective, open-label, parallel group, randomized controlled trial. This study will seek to enroll 150 healthy adults, aged from 30 to 49 years, from 2 hospitals (Kyung Hee University Korean Medicine Hospital and Kyung Hee University Korean Medicine Hospital at Gangdong, Seoul) from the Republic of Korea. The study advertisements will be posted online and offline boards. The eligible participants will then be randomly allocated to either the MBBG or control group, at a 1:1 allocation ratio. The MBBG group will then use the application for a total of 12 weeks, while the control group will receive no intervention. All the outcomes will be assessed at the baseline, week 6, and, finally, at week 12. The study procedure is summarized in Figure 1.

**Figure 1 F1:**
[figure not shown]
Study procedure. ∗Only for participants who are allocated to the intervention group. EQ-5D = EuroQoL 5-dimensional questionnaire, HRV = heart rate variability, MBBG = *Mibyeongbogam* (a mobile application), QoL = quality of life, SF-12 = short-form health survey 12-item, TKM = traditional Korean medicine.

### Eligibility criteria

2.3

Healthy male and female adults, aged from 30 to 49 years old, who are capable of using mobile smartphones are eligible for this study. They should also be able to fill in self-report questionnaires, and evaluate physical biomarkers. If the participants do not own mobile smartphones with Android version 4.4 or higher or ones with iOS version 9 or higher, they will be excluded from the screening process. Any people assessed and found to have clinically significant medical conditions, from their medical history/concomitant medication reviews and physical examinations, will also be excluded from the study. If they are already using other mobile healthcare applications, they will also become ineligible. Participants who are involved in other trials within 1 month of this one, or are pregnant at baseline, will also be considered ineligible.

The TKM doctors will obtain written consent after all information around this study have been provided to participants. Personal information, including identification codes and names, will not be recorded in the case report forms nor will they be shared with others.

### Randomization, allocation concealment, and blinding

2.4

An independent investigator will generate random sequence numbers using the R version 3.3.3 for Mac (The R Foundation) with the blockrand package, version 1.3. The random number and subsequently allocated group will then be written and delivered to each hospital via sealed envelopes. The investigators will open the envelopes in consecutive order, and assign an eligible participant to either the MBBG or the control group after a screening assessment is conducted in a 1:1 ratio. Since this is an open-label study, the participants and investigators will not be blinded. However, the outcome assessors will be blinded throughout the study to minimize possible bias.

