### Statistical analysis

2.9

The full analysis set is defined as a group including participants who are allocated to either the intervention or control group, use the MBBG application at least once, and assesses the primary outcome at least once. Per protocol set is defined as a group of the included participants who follow the trial procedure and demonstrate at least 70% compliance. The study results are analyzed primarily with the full analysis set, and subordinately with the per protocol set.

The primary variable in question is the difference in the subhealth status awareness levels between the baseline (visit 1) and the endpoint (visit 3). The mean difference will be tested using a 2-sample *t* test, or a Wilcoxon rank sum test. Any other continuous variables between the baseline and visits 2 or 3 will be tested independently, by an analysis of covariance with a covariate of the baseline values, while categorical variables will be tested by a Chi-squared or Fisher exact test. Repeated measure analysis of variance will be performed to explore any in-group differences between each of the variables throughout all visits. All of the results, analyzed with R software version 3.5.2 or later, will be addressed at a 95% confidence interval.

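### Hospital is in none of the stated models although allocation is probably balanced within it; adding it to the primary and secondary models is a small, nearly free improvement.

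*Protocol article*

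**What the plan says.** Section 2.2 of the protocol article names two recruiting hospitals under one university and 1:1 allocation.

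Section 2.4 says the sequence is generated "using the R version 3.3.3 for Mac (The R Foundation) with the blockrand package, version 1.3". It continues: "The random number and subsequently allocated group will then be written and delivered to each hospital via sealed envelopes". At the sites, "The investigators will open the envelopes in consecutive order". The section does not mention stratification by hospital, separate lists or block size.

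Section 2.9 defines the primary variable as the change in awareness score from visit 1 to visit 3. On the test it says "The mean difference will be tested using a 2-sample" t test, with a Wilcoxon rank sum test as the alternative. Other continuous variables are compared "by an analysis of covariance with a covariate of the baseline values". Categorical variables get a chi-squared or Fisher exact test, and repeated-measures ANOVA is used for changes within groups. Hospital appears in none of these.

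**The concern.** When allocation is balanced within a factor, differences between its levels cannot bias the treatment contrast and add nothing to its true sampling variance. An analysis that leaves the factor out still counts those differences as error. If the factor predicts the outcome, the estimated standard error exceeds the true one, the confidence interval is wider than it need be, and the test rejects less often than its nominal level, with some loss of power.

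Here the allocation procedure points to balance within hospital, while the fixed primary test has no place for a hospital term. What is at stake is a little precision in a trial whose planned power has no slack.

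**Working it through.** **Inputs.** From section 2.8: standardised effect d = 0.5, two-sided α = 0.05, 80% power, independent t test, 60 per group, 20% dropout, 75 per group enrolled. From section 2.2: two hospitals, 1:1. Assumed, because the article gives no figure: two equal hospitals, exact balance (30 per arm in each), a hospital effect common to both arms, and a share ρ of the variance of the change score lying between hospitals, with ρ = 0, 0.02, 0.05 and 0.10.

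**Step 1: the plan's own figure.** The dropout step reproduces: 60 / (1 − 0.2) = 75 per group. The 60 itself does not. The stated inputs give 63 per group by the normal approximation and 64 for the t test. At 60 per group, power is 78.2% (normal) or 77.5% (t test). That is a separate matter; 78.2% serves here only as the starting value.

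**Step 2: how far the standard error is overstated.** With total SD 1, the unadjusted test estimates SE = √(2/60) = 0.1826. Under balance within hospital the true SE is √(1 − ρ) × 0.1826. The ratio is k = 1/√(1 − ρ).

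**Step 3: true size of the unadjusted test.** Size = 2 × [1 − Φ(1.96 k)].

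**Step 4: power with d = 0.5 on the total SD.** Let λ = 0.5 / (0.1826 √(1 − ρ)).
- Unadjusted: 1 − Φ(1.96 k − λ).
- With hospital: 1 − Φ(1.96 − λ).

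| ρ (assumed) | Gap between hospitals in mean change, within-hospital SDs: 2√(ρ/(1−ρ)) | k | Size | λ | Power, unadjusted | Power, with hospital | Gain (points) |
|---|---|---|---|---|---|---|---|
| 0 | 0 | 1.000 | 5.0% | 2.739 | 78.2% | 78.2% | 0 |
| 0.02 | 0.29 | 1.010 | 4.8% | 2.766 | 78.4% | 79.0% | 0.6 |
| 0.05 | 0.46 | 1.026 | 4.4% | 2.810 | 78.8% | 80.2% | 1.5 |
| 0.10 | 0.67 | 1.054 | 3.9% | 2.887 | 79.4% | 82.3% | 2.9 |

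Gains are taken from unrounded powers. A simulation of 80,000 trials per setting with t tests gave power of 77.4% vs 77.4%, 77.9% vs 78.5%, 78.3% vs 79.7% and 78.8% vs 81.7%, and unadjusted size of 5.0%, 4.9%, 4.5% and 3.8%. The pattern is the same.

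**Step 5: does the scale of d matter?** If d = 0.5 is read on the within-hospital SD instead, λ stays at 2.739. Adjusted power is then 78.2% throughout, and unadjusted power is 78.2%, 77.6%, 76.7% and 74.9%. The gains are 0, 0.6, 1.5 and 3.2 points. The level moves with the reading of d; the gain hardly does.

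**The case against.** The strongest case against is that the unadjusted test is valid and that a condensed article may leave covariates and stratification to a fuller document. The validity point stands: size never exceeds 5%. The second point stands in part. The baseline value in the secondary ANCOVA is not said to be the only covariate, and silence on stratification is not itself an error. But section 2.9 does fix the primary test, and neither a two-sample t test nor a rank sum test holds a covariate. That is a stated choice, and a better one is available.

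Three stronger readings go beyond the article:
- **Separate blocked lists per hospital.** A reader might take these as a fact. They are an inference. The package, the delivery to each site and the consecutive opening make them likely, but one list divided between the hospitals also fits the text. Consecutive runs of a blocked list would still be nearly balanced. If there were no such balance, a hospital term would still guard against chance imbalance, but the argument that the test is conservative would not apply in this form.
- **Standard errors that are certainly too large.** This holds only if hospital predicts the change score. A constant difference in awareness level between hospitals cancels in a change from baseline. The hospitals share a university and eligibility criteria, and the 10% row needs mean changes 0.67 SD apart. The smaller rows, including zero, are more plausible.
- **Differences in staff education as the mechanism.** Application training goes to the MBBG group only (sections 2.5 and 2.6). Differences there would make the treatment effect vary by hospital, which is not the common shift calculated above, so the figures cannot be attributed to it.

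**Conclusion.** The point holds as a minor improvement, not as an error. Under the assumptions listed, the unadjusted primary test is slightly conservative, with size about 5.0%, 4.8%, 4.4% and 3.9% at hospital shares of 0%, 2%, 5% and 10%. A hospital term adds about 0, 0.6, 1.5 and 3 points of power. At shares up to 5%, the gain is 1.5 points at most, and it is nil if hospital does not predict change. The result rests on balance within hospital, which is probable but not stated, and on variance shares that the article does not report. The treatment comparison remains valid without the change.

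**What to change.** In section 2.9, replace the two-sample test of the primary outcome with an ANCOVA that has baseline awareness score and hospital (two levels) as covariates. Add hospital to the secondary ANCOVAs. In section 2.4, state whether the list was generated separately for each hospital.

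The cost is one degree of freedom for hospital and one for baseline in the primary model, out of 118 at 60 per group, and one for hospital in each secondary ANCOVA. Hospital and baseline score are already recorded, so only wording changes and trial conduct does not. Any precision gained from the baseline score is additional and is not counted in the figures above.

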### MBBG application for the intervention group

2.5

The Korea Institute of Oriental Medicine, in Daejeon, within the Republic of Korea, has developed MBBG, a mobile application for subhealth management. MBBG aims at assessing a user's subhealth status, as well as their TKM-based health status, which leads it to recommend specific health promoting strategies, such as meditation, exercise, and herbal teas. Patients can check their subhealth status and TKM health information after submitting all of the necessary information, including questionnaire responses. The questionnaires are included within the application, so that the participants in the intervention group can successfully complete these via the application. The examination results (height, weight, vital signs, heart rate variability [HRV], etc) have to be input into the application manually.^[6]^

After their allocation to the intervention group, participants will be educated on how to use the application, verbally, and with a user manual during every visit. They are supposed to use MBBG at least once every day for a total of 12 weeks. The push notification function will be activated to motivate the participant to use the application throughout the study period. The history tracking and user ranking services are also available to help promote the use of MBBG. Participants are not allowed to use any other mobile applications for health management during study participation.

Compliance will be calculated based on how many times participants log onto the application during the 12-week study period. The user satisfaction level will be evaluated via 10 questions at visits 2 and 3, only for participants within the intervention group.

### No intervention in the control group

2.6

Participants allocated to the control group go through the study without any intervention. They are told to maintain their usual lifestyles during the study period. They are also not supposed to use any other mobile applications for health management.

### Outcomes

2.7

Data will be recorded in the form of case reports following its collection. Personal identification information will be coded. An independent monitor will regularly visit the study sites to gauge the eligibility confirmation, source data verification, protocol deviation check, and to evaluate overall user compliance.

The data sets used and/or analyzed after completing this study will be available from the corresponding author under all reasonable requests. The investigators will disseminate the study results via publication.

#### Subhealth awareness

2.7.1

The primary outcome is the awareness of subhealth status. The participants will be given a questionnaire, consisting of 4 items: “Have you known or heard of subhealth statuses?” “Do you think that preventing diseases is as important as treating them?” “Do you think a professional medical service aimed at managing subhealth statuses is necessary?” “Are you willing to use a professional medical service to manage subhealth status, if available?” Each item is then scored from 1 (Not at all) to 7 (Absolutely), with the total score falling in the range of 4 to 28 points. The higher the score, the higher the awareness level. All participants are supposed to submit the subhealth awareness questionnaire during every visit (visits 1, 2, and 3) either via the mobile application or in a classic face-to-face fashion.

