## Discussion

3

This is a prospective, open-label, parallel group, randomized controlled trial aiming to evaluate the feasibility and effectiveness of a mobile application (MBBG) in managing subhealth statuses of healthy adults. One hundred fifty male or female subjects, without any specific diseases, will be allocated to either the MBBG or no-intervention group, with an allocation ratio of 1:1. Only the participants in the MBBG group will use the application for a total of 12 weeks. The awareness of subhealth status will be the variable primarily assessed, and changes to health promoting behaviors, QoL, TKM-based health questionnaires, and physical examination results will be also be statistically tested.

Mobile applications are a rising instrument aimed at helping people monitor their own health statuses, and in managing their own diseases, such as sleep disorders,^[18]^ diabetes,^[19]^ or even medication adherence.^[20]^ However, their effectiveness has not yet been confirmed.^[7]^ Also, no TKM-based application for health status monitoring, or subhealth management, exist. MBBG is the 1st mobile application, based on TKM theory as well as clinical research, that we expect will be feasible in the primary care for subhealth management.

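### The primary questionnaire may be answered in the app or face to face, and only the MBBG arm has the app, so mode or baseline timing can differ by arm

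*Protocol article*

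**What the plan says.** The section Subhealth awareness defines the primary outcome as the sum of four items, each rated 1 to 7, and has all participants submit it "during every visit (visits 1, 2, and 3) either via the mobile application or in a classic face-to-face fashion". It does not say who uses which mode, or that a participant keeps the same mode throughout.

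Three other sections settle who can use the app:
- MBBG application for the intervention group: "The questionnaires are included within the application, so that the participants in the intervention group can successfully complete these via the application".
- No intervention in the control group: "Participants allocated to the control group go through the study without any intervention".
- Discussion: "Only the participants in the MBBG group will use the application for a total of 12 weeks".

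On timing, the randomization section has investigators "assign an eligible participant to either the MBBG or the control group after a screening assessment is conducted in a 1:1 ratio". It does not place the visit 1 awareness form before or after that step. App training comes later and is repeated each time participants attend (the quote stops one word short of its sentence): "After their allocation to the intervention group, participants will be educated on how to use the application, verbally, and with a user manual during every".

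The Statistical analysis section then fixes the comparison: "The primary variable in question is the difference in the subhealth status awareness levels between the baseline (visit 1) and the endpoint (visit 3"), and "The mean difference will be tested using a 2-sample *t* test, or a Wilcoxon rank sum test".

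**The concern.** A randomized comparison of a questionnaire score assumes that the score is obtained in the same way in both arms and that the baseline precedes any exposure to the intervention. The rule as written secures neither. One of the two permitted modes is the intervention itself, and one arm cannot use it. An app answer at visit 1 is possible only once a participant has been allocated to the app.

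The outcome is exposed to this. Participants know their arm. Three of the four items ask for opinions or willingness concerning prevention and professional services. The other asks whether the respondent has come across the idea of subhealth before, and an explanation of a subhealth app could change that answer within minutes.

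At stake is the only primary endpoint. A difference caused by mode or baseline timing would look like an effect of the app, or would hide one. The planned unadjusted test removes neither. Adjusting for a baseline recorded after allocation would not repair it, because that baseline may itself be affected by treatment.

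**Working it through.** **Step 1. Who can use which mode.** Set side by side, the sections quoted above leave controls only the face-to-face route. MBBG participants may use either route.

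**Step 2. What remains in the change score.** Let *m* be the app-minus-face-to-face effect on the score, taken as constant over visits. Let *e* be any rise in the visit 1 score from app training given beforehand. Both are in SD of the change score. Controls are face to face at both visits, so they carry no mode term. For an MBBG participant, the amount added to the true change is:

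| Visit 1 | Visit 3 | Mode term | Baseline term |
|---|---|---|---|
| outside app | app | *m* − 0 = *m* | none arising from app use |
| app | app | *m* − *m* = 0 | −*e* if training came first |
| outside app | outside app | 0 | none arising from app use |

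For someone who answers visit 3 in the app, the mode switch and the in-app baseline are therefore alternatives. They do not add up. The last row is clean only if the visit 1 form also precedes allocation, which the text does not state.

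The arm-level shift *b* is the average over MBBG participants. If half of them switch mode and the rest carry no shift, *b* = 0.5 × *m*, so *b* = 0.2 would need *m* = 0.4.

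**Step 3. The plan's own sample size.** Inputs from Hypothesis and sample size calculation: effect size 0.5, two-sided α 0.05, power 0.8, 60 per group, 20% dropout.
- The dropout step reproduces: 60 / 0.8 = 75 per group, 150 in total.
- The 60 does not. The independent *t* test needs 63.77, so 64 per group. With 60 per group, power is 77.5%. That is a separate matter. It is noted here only because 77.5% is the reference value below.

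**Step 4. What a net shift would do.** The documents give no size for *b*, so 0.1, 0.2 and 0.3 SD are assumptions. With n = 60 per arm there are 118 degrees of freedom, and the noncentrality is δ√(n/2) = δ√30, where δ is the standardized difference that the test sees. The rejection probability is that of a noncentral *t* exceeding the two-sided 5% critical value in absolute size.

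| Assumed net shift *b* | Rejection rate, no true effect (δ = *b*) | Power at true 0.5 if the shift works against MBBG (δ = 0.5 − *b*) |
|---|---|---|
| 0 | 5.0% | 77.5% |
| 0.1 | 8.4% | 58.4% |
| 0.2 | 19.2% | 37.1% |
| 0.3 | 37.1% | 19.2% |

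The two columns share values because δ = 0.2 and δ = 0.3 occur in both.

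**The case against.** The strongest reply is that the text permits and does not prescribe. The mode rule assigns nothing by arm, and the intervention section says only that MBBG participants are able to answer in the app. All of them might answer at the clinic, with visit 1 before allocation, and then the problem does not arise. This stands as a limit on the wording: the plan allows arm-dependent collection and does not order it. It is no defence of the rule, because nothing in the article excludes the problematic cases.

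Second, the primary variable is a change score, so a mode effect present equally at visits 1 and 3 cancels. This is correct. It rescues only participants who use the app at both visits, and their baseline then follows allocation.

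Third, the order of procedures at visit 1 is not stated. Even an in-app form could be completed before training, and Figure 1, which is not shown, may settle the sequence. This stands too: a baseline after training is a possibility only.

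Fourth, face to face may mean a form that participants complete themselves and hand in, since eligibility requires that they can fill in self-report questionnaires. A reader might infer that controls are interviewed by staff and that social desirability drives their answers. The documents do not support going that far. Without an interviewer the mode effect may be smaller, but the app still remains a mode for one arm only.

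**Conclusion.** The point holds as a weakness in a stated rule. As written, the plan lets the mode of collecting the sole primary outcome differ by arm. For any MBBG participant who answers visit 3 in the app, either the mode changed between baseline and endpoint in that arm only, or the baseline was recorded after allocation and possibly after training.

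The size and direction are unknown. The figures of 8%, 19% and 37% for rejection under no effect, and 58%, 37% and 19% for power, rest on assumed net shifts of 0.1, 0.2 and 0.3 SD in the change score with 60 evaluable per arm. They show what such a shift would do, not how likely it is.

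A reader might infer three stronger things: that the MBBG arm always answers in the app and has a contaminated baseline, that both mechanisms act together in the same person, or that the trial's error rate is actually inflated to these levels. The documents support none of them. App use is optional in the text, the two mechanisms are alternatives for a participant who ends in the app, and a constant mode effect leaves the error rate at 5%.

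**What to change.** Collect the awareness score on one identical self-completed form, on paper or a clinic tablet outside the app, for both arms at visits 1, 2 and 3. State that the visit 1 form is completed before the randomization envelope is opened. Use the questionnaires inside the app only to drive its recommendations, not as trial outcome data. Applying the same rule to the other self-report outcomes would be consistent.

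This needs a short protocol amendment. The burden is a little duplicate entry: MBBG participants fill in a 4-item form at visits they already attend. The sample size and the planned test need no change on this account.
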